# Evaluation of 24-Month Effects of the Close to Home Program on Youth Sexual and Dating Violence Across 22 Communities in California: Protocol for a Quasi-Experimental Cluster-Matched Control Trial

**DOI:** 10.2196/81249

**Published:** 2026-07-15

**Keywords:** research design, matched groups, intimate partner violence, primary prevention, social norms, sexual harassment, violence, adolescents, United States

## Abstract

**Background:**

Sexual violence (SV; any sexual activity where consent is not obtained or freely given) and dating violence (DV; abuse or aggression that occurs in a romantic relationship among youth) are interrelated public health concerns among youth in the United States. Despite its urgency, there is a dearth of comprehensive SV and DV prevention approaches that intervene across multiple social ecology levels (ie, at the individual, interpersonal, community, and societal levels). Therefore, the field of violence prevention has called for the development and evaluation of community-level interventions for prevention. Close to Home (C2H) is a community-driven community mobilization primary prevention program that aims to have community-level effects on reducing SV and DV, as well as improving community connection and social norms related to SV and DV, yet it has never been rigorously evaluated.

**Objective:**

This research study aimed to rigorously evaluate the C2H model at three levels of the social ecology (individual, interpersonal, and community) in 22 diverse communities in California.

**Methods:**

This protocol outlines a quasi-experimental cluster-matched control trial to evaluate the 24-month effects of C2H on SV and DV among youth ages 14‐24 years. The study used a social network (SN) sampling design to assess the diffusion of intervention effects across youth and their SNs, as well as community-wide school-based data from the California Healthy Kids Survey to provide critical evidence on the effectiveness of community mobilization as a viable community-level approach for SV and DV prevention. Primary outcomes included experiencing SV and DV with a 12-month incidence for youth ages 14‐24 years, including sexual assault, in-person and online sexual harassment, and DV. Secondary outcomes included protective social norms rejecting SV and DV and community connection. Further, 11 preselected implementation sites from across California participated in the evaluation and were matched with 11 control program sites based on key demographics and county-level factors related to SV.

**Results:**

This study was funded in September 2020, and institutional review board approval was obtained in February 2021. Baseline survey data were collected on a rolling basis between October 2021 and June 2023 from 953 participants of the SN sample. Follow-up survey data were collected from September 2023 to November 2025 from 746 participants. Data analysis will be conducted from summer to fall 2026. Study findings will be published in late 2026.

**Conclusions:**

This study is among the first to rigorously evaluate a community mobilization approach to SV or DV prevention in the United States. The evidence will support community-level approaches to address the high prevalence of SV and DV in US youth populations, and this study was developed in response to the field’s call for further investigation of prevention strategies that address prevention at the outer levels of the social ecological model (ie, community and societal-level prevention).

## Introduction

Sexual violence (SV; any sexual activity where consent is not obtained or freely given) [1] and dating violence (DV; abuse or aggression that occurs in a romantic relationship) [2] are prevalent and interrelated public health concerns among youth in the United States. Experiencing SV or DV during the developmental period of adolescence has been shown to increase risk for lower educational attainment [3-5], continued experiences of violence [6,7], poor cognitive function, substance use, disordered eating, poor mental health, and suicide [8-10]. Data from the 2023 Youth Risk Behavior Survey, the most recent nationally representative youth sample, show that 11.4% of youth (ages 13 to 18 years) in the United States report past 12-month experiences of SV, 5.9% report past 12-month experiences of sexual DV, and 10.4% report past 12-month experiences of physical DV [11]. Disproportionately high prevalences of SV and DV are experienced by female youth (17% SV, 9.3% sexual DV, and 11.4% physical DV) and sexual and gender minority (LGBTQ+) youth (20.3% SV, 10.7% sexual DV, and 17.6% physical DV) [11]. While both SV and DV are preventable, evidence-based approaches to reducing SV and DV prevalence among youth at the population level are limited.

Primary prevention approaches that aim to prevent SV or DV among youth have primarily focused on individual-level or school-based approaches [12-16]. SV and DV are complex public health problems, and there is a growing consensus that multilevel interventions, including community-level prevention strategies, are necessary [17]. Despite decade-old federal recommendations to target social norms and create protective environments to effectively prevent SV and DV, there is a limited number of community- or societal-level evidence-based SV or DV prevention approaches in the United States [15]. In response to this gap, the field has called for the development and evaluation of community-level interventions to prevent SV and DV [17-19].

Evidence suggests that community mobilization may be a promising strategy for multilevel SV and DV prevention. Community mobilization is a dynamic process of community organizing that mobilizes community members and existing resources to create community-led change [20]. There is evidence of community mobilization’s positive effects on adolescent pregnancy [21], HIV testing and safe sex practices [22,23], gang violence [24], and suicide [25]. Worldwide, particularly in sub-Saharan Africa, multiple community mobilization models designed to reduce SV or DV have shown positive effects [26-28]. These community mobilization strategies are hypothesized to have effected reductions in SV and DV by targeting social norms around the acceptability of violence and gender expectations and strengthening community connection and trust. Given this related evidence, the potential for community mobilization to have an impact on SV and DV in the United States is strong, but evaluation research is needed.

Close to Home (C2H) is a community mobilization SV primary prevention program that mobilizes youth and adults to catalyze community-driven violence prevention through promoting protective social norms and environments. The C2H model was developed to address SV specifically based on the learnings from evidence-based SV and DV community mobilization models shown to be effective in sub-Saharan Africa [26-28]. First developed by grassroots community organizers for implementation in the community of Dorchester, Massachusetts, C2H was chosen in 2008 as a promising violence prevention strategy to be implemented in 3 Massachusetts communities in partnership with the Massachusetts Department of Public Health and in 10 communities in California in partnership with the California Department of Public Health (CDPH). From 2019‐2024, a total of 12 nongovernmental organizations (NGOs) across California received funding to implement C2H in their community, presenting a unique opportunity for evaluating the effect of community mobilization on SV and DV in the United States.

With funding from the Centers for Disease Control and Prevention (CDC) and in partnership with CDPH’s SV prevention program, we conducted a quasi-experimental, parallel group, cluster-matched control trial of C2H across 22 communities from 2020 to 2026. A priori, primary outcomes included experiences of SV and DV, and secondary outcomes of social norms change related to SV and DV and community connection. The evaluation was designed to assess effects at the individual, interpersonal, and community level by using a social network (SN) sampling design to assess diffusion of intervention effects across youth participants of the program and their SNs, as well as community-wide school-based data.

## Methods

### Ethical Considerations

Ethics approval was obtained from the University of California (UC), San Diego Human Research Protections Program (HRPP) under protocol #201920. Subsequently, UC Davis (1797611-2, reliance agreement 201920S) and UC Berkeley (SMART IRB 201920) approved to rely upon the UC San Diego HRPP approval. This study’s protocol was granted a waiver for parental consent for participation in the SN data collection, and informed consent or assent was obtained from all youth and young adult SN participants. Informed opt-out parental consent and youth assent were obtained for the California Healthy Kids Survey data collection. No later than 3 years after data collection is complete, we will put a completely deidentified data set on an appropriate data archive platform for sharing purposes. Participating pilot testers, egos, and nominated alters 1 and 2 provided assent for participation and were compensated either US $20 (ego and alter 1) or US $25 (alter 2) for participating in the survey and US $10 for each nominated peer who opted in to learn more about the survey. We obtained ethical approval with a waiver of parental consent from HRPP.

### Setting

California is a large and diverse state, with SV and DV prevalences that are similar to national prevalences [29,30]. Since 2010, with funding from CDC, CDPH has supported and monitored the statewide implementation of C2H as part of CDPH’s Rape Prevention and Education (RPE) Program and has developed extensive state-level training and technical assistance (TTA) infrastructure, as well as standardized programmatic and evaluation materials to support high-fidelity implementation of the C2H model. In 2018, CDPH’s RPE Program held an open request for funding proposals and selected 9 NGOs for funding to implement C2H over a 5-year grant period from 2019 to 2024. Funded organizations all prioritized populations that are disproportionately impacted by SV, including non-English speaking populations, rural communities, and gender and sexual minorities. A total of 8 of the 9 CDPH-funded sites agreed to participate in the evaluation, and 1 site was excluded from eligibility due to incomplete adherence to the C2H model. Between 2021 and 2022, a total of 3 additional implementation sites received other external grant funding to implement C2H, 2 of which were organizations funded by CDPH to implement C2H in different geographical communities, and agreed to participate in the evaluation. In total, 11 California communities implementing C2H projects were selected a priori as intervention sites for this evaluation (Figure 1).

**Figure 1. F1:**
[figure not shown]
Map of Close to Home intervention sites.

### Intervention Sites

Each of the 11 C2H intervention sites defined the geography of the implementation community by a target zip code and a high school within the target zip code. Of the 11 implementation communities, 8 communities served predominantly non-English speaking populations, 8 communities served communities where the majority of the residents were marginalized racial or ethnic minorities, 3 communities served rural communities, 6 communities served communities with incomes below the federal poverty line, and 2 communities focused on serving gender and sexual minorities. Participating communities were located across northern, central, and southern regions of California (Figure 1). Each site began a new cycle of C2H implementation between mid-2021 and 2022, after baseline data collection.

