#### SN Primary Data Collection

##### Youth Recruitment

Youth program participants ages 14‐24 years were recruited to this study from each C2H site and the matched control site within 6 months of one another (henceforth, “egos”). Ego recruitment was initiated at a C2H site as soon as the site had recruited and established a youth team to begin a new cycle of C2H implementation, between October 2021 and May 2023. Due to major disruptions caused by the COVID-19 pandemic, C2H implementation began at different time points across sites; 7 sites started in the fall of 2021 and 4 sites started in the fall or winter of 2022‐2023.

To recruit youth, the cofirst author attended a regular C2H/4-H meeting (in-person or virtual), shared this study’s purpose, the SN recruitment process, the risks and benefits of participating, compensation, and, after all questions were answered, invited youth to participate in this study. Those who were interested in participating were sent a personalized link using a provided phone number or email address. Research staff provided tablet devices, device chargers, a Wi-Fi hotspot, and snacks to participants as needed. After this initial meeting, as new youth were recruited to the C2H/4-H groups, research staff continued recruitment as needed, providing virtual or in-person survey orientations as needed to invite all C2H/4-H members to participate and maximize ego recruitment.

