## Results

This study was funded in September 2020 for three years and was given two additional years of funding through a competitive renewal (through September 2025). A no-cost extension was granted through September 2026. Institutional review board approval was granted in February 2021. Baseline survey data were collected on a rolling basis between October 2021 and June 2023 from 953 participants of the SN sample. Baseline data were analyzed in 2025, and results related to the SN structure are expected to be published in the fall of 2026. Follow-up survey data were collected from September 2023 to November 2025 from 746 participants. Main effect analysis will take place from summer to fall 2026. Main effect findings will be published in late 2026 or early 2027.

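### Some Close to Home baseline surveys may postdate the program's start: the stated dates conflict, and no listed sensitivity analysis covers an exposed baseline

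*Protocol article*

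**What the plan says.** The Protocol article dates the start of Close to Home (C2H) and the social network (SN) baseline in several places.

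- Intervention Sites: "Each site began a new cycle of C2H implementation between mid-2021 and 2022, after baseline data collection".
- Results (and the Abstract): "Baseline survey data were collected on a rolling basis between October 2021 and June 2023 from 953 participants of the SN sample".
- Youth Recruitment, on starts: "7 sites started in the fall of 2021 and 4 sites started in the fall or winter of" 2022-2023.
- Youth Recruitment, on the trigger for enrolment: "Ego recruitment was initiated at a C2H site as soon as the site had recruited and established a youth team". The same sentence carries the window October 2021 to May 2023.
- Youth Recruitment, on later joiners: "as new youth were recruited to the C2H/4-H groups, research staff continued recruitment as needed". No cut-off at program start is given. Nominated peers are surveyed after the person who nominated them.
- Strengths and Limitations: baseline and program initiation are both placed in 2021-2023, with no order.

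Intervention Description puts training on the causes of violence before the four program phases. Follow-Up SN Data Collection says the phases need at least 12 months and that follow-up came 24 months after baseline. Analysis of SN Data makes adjusted hierarchical difference-in-differences the main analysis. Its sensitivity analyses cover parallel trends, response rates and loss to follow-up. None covers baselines taken after the program began.

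**The concern.** Difference-in-differences subtracts a before-measurement. The article relies on this heavily: Analysis of SN Data argues that the method offsets the three poor control matches because it accounts for baseline differences. That argument needs a baseline the program has not yet touched.

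The one sentence that asserts this order conflicts with the other dates. The recruitment rule also allows later baselines. Egos had to be current members of a formed team, and enrolment stayed open as new members joined. If C2H is beneficial, part of its effect would sit in those participants' baseline values, be subtracted out, and pull the estimate toward no effect.

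Only two SN waves are described, so these data offer no earlier wave against which to check the baseline. The planned group-weighting sensitivity analysis for staggered timing needs a start date for each site, which is the item left inconsistent.

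**Working it through.** **1. Dates.** No site-level dates are given, so only the stated windows can be compared.

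| Comparison | Months |
|---|---|
| Mid-2021 start (June or July) to first baseline survey (October 2021) | 4 or 3 |
| End of the stated start window (December 2022) to last stated C2H ego recruitment (May 2023) | 5 |
| December 2022 to last baseline survey (June 2023) | 6 |
| Whole baseline window (October 2021 to June 2023) | 20 |

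A site that started in mid-2021 cannot have started after a baseline that opened in October. At the other end, the May 2023 date belongs to a sentence about C2H sites. If it dates recruitment, enrolment at C2H sites was opening up to 5 months after the last start allowed under Intervention Sites. If it dates cycle starts, the 2022 limit is wrong. The Intervention Sites sentence fails on either reading. Winter 2022-2023 can also run past 2022.

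**2. What cannot be computed.** The number of C2H baselines taken after their own site's start is unknown. Enrolment was rolling by site, so a 2023 survey at a late-starting site may precede that site's start, and some late surveys may come from control sites.

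**3. Illustrative size, past-12-month sexual violence.** The plan gives no figure for this point. Its planned effect (SN Data Statistical Power) is 0.27 × 0.32 = 0.0864, or 8.64 points. Let f be the share of C2H baselines taken after start and w the months of the 12-month recall already exposed; both are assumptions. If the full effect acts at once in exposed months,

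estimate = 0.27 × 0.32 × (1 − f × w/12).

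Power is calibrated to the plan's 0.80 at the full effect, which for 27% versus 18.36% corresponds to an effective 368 per arm.

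| f | w | 1 − f × w/12 | Estimate (points) | Power |
|---|---|---|---|---|
| 0 | – | 1.000 | 8.64 | 0.80 |
| 10% | 3 | 0.975 | 8.4 | 0.78 |
| 25% | 3 | 0.938 | 8.1 | 0.74 |
| 25% | 6 | 0.875 | 7.6 | 0.68 |
| 50% | 6 | 0.750 | 6.5 | 0.54 |

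For given f and w this is an upper bound on the loss, because the program builds up over at least 12 months.

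**4. Current-state outcomes.** Attitudes, norms, confidence and connection have no 12-month recall to dilute early exposure. If exposed baselines already carry a share s of the effect, the fraction recovered is 1 − f × s. With f = 0.3 and s = 0.5 it is 0.85; with f = 0.5 and s = 0.5 it is 0.75. Both inputs are again assumptions.

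**5. The gap within pairs.** C2H and matched control sites were recruited "within 6 months of one another". Follow-up is 24 months after each participant's own baseline, so the gap carries to both waves and a constant linear trend cancels. A residual bias needs the trend to change. For example, a rise of 4 points a year before baseline that is flat by follow-up gives 0.5 × 4 = 2 points in a pair at the full 6 months. One such pair among 11 equally weighted pairs adds 2/11, about 0.2 points; the full 2 points needs all 11 at the maximum and in the same direction.

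**The case against.** The strongest reply is that the clash may be loose dating in one sentence. A fall 2021 start fits a baseline opening in October 2021, and recruitment was tied to each site's own team formation. This stands as far as it goes: the documents do not show how many baselines followed start.

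A reader might infer that many baseline surveys were exposed and that the pre-period is contaminated. The documents do not support that without site-level dates. The primary outcome looks back 12 months and public campaigns come in the last phase, so a survey soon after start describes mostly unexposed time, especially for peers outside the program.

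A reader might also treat the 6-month pair gap as contamination. It is a maximum, it affects calendar time rather than exposure, and the 2-point figure is a worst case. Strengths and Limitations assumes that the pandemic affected both arms similarly; this is untested, but nothing shows the contrary.

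Finally, a reader might infer earlier C2H cycles from the funding history ("selected 9 NGOs for funding to implement C2H over a 5-year grant period from 2019 to 2024") and the reference to a new cycle. No earlier cycle is documented in these communities, and three sites obtained their funding only in 2021-2022.

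The planned dosage, as-treated and staggered-timing analyses bear on timing and trends. They do not repair a baseline measured after exposure. Whether the model has a survey-date term may be left to the full analysis plan, so its absence from the article is not a fault.

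**Conclusion.** The point holds in a limited form. The statement that every site started after baseline conflicts with the article's own dates, and the enrolment rule lets some C2H baselines, number not stated, follow training or program activity. The direction is toward no effect if C2H is beneficial. Current-state secondary outcomes are the more exposed; past-12-month violence is less so.

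The size is not known. The range of 8.4 down to 6.5 points against 8.64 rests on assumed f and w and on an immediate full effect. The date conflict rests on no assumption. The matter should be settled before the main analysis, which Results places in summer to fall 2026, but it does not call for a different primary model.

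**What to change.** 1. Reconcile the timing statements in Intervention Sites, Youth Recruitment, Results, and Strengths and Limitations.
2. From process data and survey timestamps, tabulate by site and arm the baseline survey dates against the date of the first C2H training or session. The monthly staff surveys should supply the latter. Survey dates must have been held, since follow-up was timed from each participant's own baseline.
3. Pre-specify a sensitivity analysis that flags or excludes baselines taken after site start, applying the matched C2H site's window to its control.
4. Pre-specify a second that adjusts for calendar time of survey.
5. If process data show C2H activity in a community before baseline, state the estimand there as the effect of the new cycle.

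The cost is programming on records that should already exist. Excluding late joiners and their peers loses precision and may introduce selection, and controls have no true start date, only a borrowed one. With 22 sites surveyed on a rolling basis, calendar time may also be partly confounded with site. Both analyses should therefore stay as sensitivity analyses, with the primary model unchanged.

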### Intervention Description

The C2H model provides a framework and process for mobilizing community members to engage in community-led SV prevention. After recruiting teams of youth and adult community members and training them on root causes of SV and DV and skills for community organizing, the teams (henceforth, “the network”) move through four phases: assess, talk, build, and act. In the assess phase, the network uses a community mapping tool to determine the driving factors of SV in the community and to formulate learning questions that the network intends to answer. In the talk phase, the network engages additional community members in conversations about SV through small group community dialogues (called “kitchen table talks”), art and storytelling, and attending public meetings, including community coalition meetings and community meetings with local civic leaders. The purpose of these discussions is to break the silence around SV by sharing stories and experiences to form a shared, public analysis of SV and why it happens, to create energy for community change, and to expand the network by recruiting additional community members to join in a shared vision for change. In the build phase, the network forms project teams to develop plans, develop skills, and gather resources for designing community actions and campaigns to prevent SV based on the vision developed in the talk phase. In the act phase, the work of the previous phases culminates in network members leading community actions and campaigns designed by the network members to reduce SV. These public actions and campaigns were intended to attract even more community members to the network to grow its momentum toward community-level change. Cyclical in nature, the C2H process may then repeat with the expanded network of community members. Participants could withdraw from the program at any time.

C2H was hypothesized to create impact at the individual, interpersonal, and community levels based on the Theory of Bounded Normative Influence (BNI) [31,32], a theory of social norms change via SNs that is rooted in the principle of Diffusion of Innovation [33], and the Theory of Planned Behavior (TPB) [34]. Based on TPB, at the individual-level, C2H was hypothesized to increase knowledge about SV and DV and social capital, then shift behavioral attitudes, perceived social expectations regarding SV and DV (ie, subjective norms) within the C2H network, and perceived behavioral control. These changes, in turn, influence behavioral intentions and subsequently, behavior to be more protective against SV and DV. At the interpersonal and community levels, based on BNI, C2H was hypothesized to change SV and DV social norms and increase community connectivity to prevent SV through social diffusion, as illustrated in Figure 2. Within a given C2H network, a subset of the local community population, we expected that most individual network members would shift their individual-level beliefs and attitudes to be more protective against SV (based on TPB), despite community members outside of the network possibly holding other beliefs or attitudes (right side of Figure 2, circle 1, white dots). As the C2H community-led actions were implemented across the community, community members outside the network who are reached by these actions would increase their knowledge about SV and DV, shift their SV and DV–related attitudes to be more similar to those of the C2H network, and will develop authentic connections with members of the expanding C2H network, as a result of interacting with network members and their C2H actions. Those community members reached by the C2H actions would become an increasingly larger subset of the community population as more C2H actions are implemented. “Reached” community members would, in turn, influence the knowledge, attitudes, and perceived subjective norms of other community members they had preexisting relationships with to be more protective against SV and DV (circle 2) until the subpopulation holding these protective SV and DV attitudes, previously a minority group in the larger community, becomes a majority within the broader community (circle 3). Through the ongoing, active efforts of C2H participants to increase knowledge, shift attitudes, set new social expectations (ie, social norms) regarding SV and DV, and build connections across community networks, broader social norms change across the community was expected. Additional details on the C2H model can be found online [35].
